### 9.3 Secondary analyses

#### Sustainable effectiveness

Sustainable effectiveness is defined as a significant improvement in  $VO_{2peak}$  level from baseline (T0) to 12 months after start of CR programme (T2). Differences between intervention groups in sustainable effect will be analysed in similar linear mixed models comparing the difference between change in  $VO_{2peak}$  from T0 to T2 adjusting for baseline values of  $VO_{2peak}$ .

Differences between intervention groups in any of the outcome measures over time will be examined using mixed models repeated measures analysis (MMRM) with intervention group and time points as fixed effects and centre as random effect and baseline values as covariate. When necessary the outcome variables will be transformed to obtain a normal distribution. The null hypothesis is that the outcome under study is the same at all time points (T0, T1 and T2). The alternative hypothesis is that the outcome under study at at least one of the time points differs from the others. We will test for the interaction between intervention and time in order to investigate whether the development of study parameters over time differs between interventions. A two-sided p-value of less than 0.05 for a coefficient will be considered to be statistically significant. If the results of the MMRM analysis are statistically significant, we will run post hoc tests to highlight where these differences occur, adjusting the p-value for multiple comparisons using the Tukey procedure.

Differences between intervention groups in utilisation of medical care will be tested by linear mixed models with centre as random effect for continuous outcome or mixed models for logistic regression for dichotomous outcomes. When necessary continuous outcome variables will be transformed to obtain a normal distribution.

The cumulative incidences of the composite endpoint MACE and the elements from which it is constituted will be presented by intervention group. We will compute the probability of survival free from MACE past given time points (6 months and 1 year) and the survival function will be plotted by intervention group in Kaplan-Meier survival curves. The Kaplan Meier curves will indicate the occurrence of MACE during 1 year of follow-up. Patients who do not experience an event or are lost to follow-up without an event are censored.

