## Abbreviations

|      |                                             |
|------|---------------------------------------------|
| ACS  | Acute coronary syndrome                     |
| AE   | Adverse event                               |
| BIC  | Bayesian information criterion              |
| BMI  | Body mass index                             |
| CABG | Coronary artery bypass grafting             |
| CAD  | Coronary artery disease                     |
| CCR  | Costs for cardiac rehabilitation            |
| CCS  | Canadian Cardiovascular Society             |
| CCU  | Costs for care utilization                  |
| COPD | Chronic obstructive pulmonary disease       |
| CPET | Cardiopulmonary exercise test               |
| CR   | Cardiac rehabilitation                      |
| CRTP | Cardiac resynchronization therapy pacemaker |
| CV   | Cardiovascular                              |
| CVA  | Cerebrovascular accident                    |
| CVD  | Cardiovascular disease                      |
| FEV  | Forced expiratory volume                    |
| GCP  | Good clinical practice                      |
| HDL  | High-density lipoprotein                    |
| HSD  | Honestly significant difference             |
| ICD  | Implantable cardioverter-defibrillator      |
| ICER | Incremental cost effectiveness ratios       |
| LDL  | Low-density lipoprotein                     |
| LVEF | Left ventricular ejection fraction          |
| MACE | Major adverse cardiovascular events         |
| MI   | Myocardial infarction                       |
| MMRM | Mixed models repeated measures              |
| NYHA | New York Heart Association                  |
| OR   | Odd ratio                                   |
| OSA  | Obstructive sleep apnea                     |
| PCA  | Principal component analysis                |
| PCI  | Percutaneous coronary intervention          |
| RCT  | Randomised controlled trial                 |
| RER  | Respiratory exchange ratio                  |
| SAE  | Serious adverse event                       |
| SAP  | Statistical analysis plan                   |
| TAVI | Transcatheter aortic valve implantation     |
| TC   | Total costs                                 |
| TIA  | Transient ischemic attack                   |

[figure not shown]**Definitions**

Definitions are captured in a separate document "EU-CaRE & EU-CaRE RCT SAP definitions" with version 1.0; 05 July 2017.

[figure not shown]

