Additionally, we will perform a mixed models repeated measures (MMRM) analysis with intervention effect and time points as fixed effect and centre as random effect and baseline value as covariate. When necessary the outcome variables will be transformed to obtain a normal distribution. The null hypothesis is that the outcome under study is the same at all-time points (T0, T1 and T2). The alternative hypothesis is that the outcome under study at least one of the time points differs from the others. A covariance structure will be selected from several plausible structures. The covariance matrix resulting in the lowest BIC fit statistic will be chosen. We will test for the interaction between intervention group and time in order to investigate whether the development of study parameters over time differs between the interventions. A two-sided p-value of less than 0.05 for will be considered to be statistically significant. If the results of the MMRM analysis are statistically significant, we will run post hoc tests to highlight where these differences occur, adjusting the p value for multiple comparisons using the Tukey procedure.

[figure not shown]

## 7. Study objective 3

Joining the *mCR* programme results in improved traditional risk profile (i.e. lipid profile, HbA1C, lean body mass, blood pressure) in cardiac patients in comparison to not joining the *mCR* programme after 6 (T1) and 12 months (T2).

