### *Outcomes*

#### Cardiovascular risk factor control:

- Changes in lipid profile (T1-T2)
- Changes in HbA1C (T1-T2)
- Changes in lean body mass (T1-T2)
- Changes in blood pressure (T1-T2)

The differences between the randomisation groups on the secondary continuous outcomes will follow the same approach as described in section 6 Study objective 2.

All analyses of PP will be in parallel to the description of the above.

[figure not shown]

## 8. Study objective 4

The overall occurrence of MACE (cardiovascular mortality, all-cause mortality, near sudden cardiac death, ACS, CV intervention/surgery, CV hospital admission, CV emergency visit) in the intervention group is lower than in the control group at T1 and T2.

The cumulative incidences of the composite endpoint MACE and the elements from which it is constituted will be presented by group. We will compute the probability of survival free from MACE past given time points (6 months and 12 months) and the survival function will be plotted by intervention group in Kaplan-Meier survival curves. The Kaplan Meier curves will indicate the occurrence of MACE during 12 months of follow-up. Patients who do not experience an event or are lost to follow-up without an event are censored. We will test for differences in hazard rates between the *mCR* and control group using Cox regression analysis allowing the baseline hazard functions to differ between centres.

[figure not shown]

## 9. Study objective 5

Joining the *mCR* programme results in an improved general health (e.g. quality of life (SF-36v2: Physical and Mental Component Summary Score), level of depression (PHQ-9), level of anxiety (GAD-7) and dietary pattern (Mediterranean Diet Score)) in comparison to not joining the *mCR* programme after T1 and T2 in cardiac patients.

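### The Tukey post hoc step of the supplementary MMRM has no defined family or gate, omits the arm difference in T2-T1 change on the usual reading, and costs power, mainly for the objective 3 risk factors

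*Combined protocol and SAP*

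**What the plan says.** SAP section 6 (Study objective 2) first tests the arm difference in T2-T1 change in VO2peak in its own linear mixed model. Centre is random, the T1 value is a covariate, and there is no multiplicity step. It then adds an MMRM with "centre as random effect and baseline value as covariate". The null written for the MMRM concerns time, not arms: "The null hypothesis is that the outcome under study is the same at all-time points (T0, T1 and T2". The section continues, "We will test for the interaction between intervention group and time", and then sets the post hoc rule: "If the results of the MMRM analysis are statistically significant, we will run post hoc tests to highlight where these differences occur". For these tests the SAP prescribes one correction, namely "adjusting the p value for multiple comparisons using the Tukey procedure".

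Protocol 9.3 has the same rule for any outcome measure, "adjusting the p-value for multiple comparisons using the Tukey procedure". In SAP section 7 (objective 3: lipids, HbA1c, lean body mass, blood pressure) the continuous outcomes "will follow the same approach as described in section 6 Study objective 2". The SAP abbreviation list expands HSD as "Honestly significant difference", which points to the all-pairwise form of Tukey. Neither document lists the means to be compared, the contrasts of interest, or the MMRM effect that must be significant.

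**The concern.** The purpose of the step is to show where the arms differ. Tukey's procedure protects all pairwise differences among a set of means. With arm-by-time cells as the means, most of those pairs are not treatment comparisons, yet they set the threshold for the few that are. The arm difference in change between T1 and T2 is a difference of differences, so it is not a pair at all.

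The gate is also open to interpretation. A step opened by a significant time effect protects nothing about the arms. What is at stake is a lower chance of locating a real arm difference at T1 or T2 where this step is the planned model-based route to it, and an analyst left to choose the family and the gate after seeing data.

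**Working it through.** **Inputs.** SAP section 3 and protocol 5.4 give an arm difference of 3.0 ml/kg/min, SDs of 5 and 6, two-sided 0.05, 80% power, ICC 0.05 and 30% withdrawal.

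**The plan's own figure.**
- With variance sum 25 + 36 = 61, noncentral-t power is 0.799 at 54 per arm and 0.806 at 55, so 55 is reproduced.
- 55 × [1 + (11 − 1) × 0.05] = 82.5, rounded to 83. The cluster size of 11 is inferred; 55/6 would give 78.
- 83/0.70 = 118.6, rounded to 119.

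Below, 55 is the size before centre inflation and 83 is the number left after withdrawal.

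**What an all-pairs family contains.** The SAP has baseline as a covariate but also names T0 as a time point, so two readings are possible.

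| Reading | Cells | Pairs | Arm pairs at T1, T2 | Arm pair at T0 | Within-arm pairs | Cross-cell pairs |
|---|---|---|---|---|---|---|
| T1, T2 as outcomes | 4 | 6 | 2 | none | 2 | 2 |
| T0, T1, T2 as outcomes | 6 | 15 | 2 | 1 | 6 | 6 |

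The contrast (mCR T2 − mCR T1) − (control T2 − control T1) involves four cells, so it is in neither set.

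**Critical values.** Tukey |t| = q(0.95; k, 160)/√2. This gives 2.596 for k = 4 (nominal p about 0.010) and 2.885 for k = 6 (about 0.004), against 1.96 unadjusted. Large-sample values are slightly lower, 2.57 and 2.85.

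**Power for one arm contrast.** Power = Φ(3/√(61/n) − critical value). The first term is 2.849 at n = 55 and 3.499 at n = 83.

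| n per arm | Unadjusted | Tukey, 4 cells | Tukey, 6 cells |
|---|---|---|---|
| 55 | Φ(0.889) = 81% | Φ(0.253) = 60% | Φ(−0.036) = 49% |
| 83 | Φ(1.539) = 94% | Φ(0.903) = 82% | Φ(0.614) = 73% |

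**Is Tukey needed to control error?** Of the three arm contrasts (T1-T0, T2-T0, T2-T1), any two being null makes the third null. A level-0.05 gate on the joint arm effect followed by each contrast at 0.05 is therefore a closed procedure. I simulated it with 400,000 draws per setting and assumed correlations of 0.3 to 0.8 between the T1 and T2 arm contrasts. With no arm effect, the chance of any false arm finding is 5.0% with a 2-df joint arm gate. It is about 12% if the gate says nothing about arms, as when a time effect alone opens it.

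**Power including the gate.** The gate has its own cost. At 55 per arm, with correlations of 0.3 to 0.7 and a T2 effect of zero, half or equal to that at T1, the chance of passing the gate and declaring the T1 contrast is about 71% to 81%. The Tukey figures stay at about 60% and 49%, because a result that clears the Tukey threshold nearly always passes the gate too.

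**Which gate.** If only T1 and T2 are outcomes, the intervention-by-time test has 1 df and is the T2-T1 contrast itself. A benefit equal at T1 and T2 gives no interaction, so that gate opens only about 5% of the time. The joint test of the two arm differences is needed in that case.

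**The case against.** The strongest reply is that the MMRM is explicitly additional. For VO2peak, SAP sections 5.1, 5.2 and 6 each give a dedicated mixed model, for T1-T0, T2-T0 and T2-T1, with no Tukey step. A reader might infer that objective 2 goes untested or that real VO2peak differences will be missed; the documents do not support that. Section 7 takes over the whole of section 6, including the dedicated T2-T1 model, and the changes it lists are all T1-T2. Protocol 9.1 also plans unadjusted t-tests between arms at 6 and 12 months. All of this stands and confines the problem. It does not remove it: objective 3 claims benefit at T1 and at T2, protocol 7.2.1 lists T1-T0 and T2-T0 changes for these risk factors, and within the SAP the MMRM step is the only model-based route to those arm differences.

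A second reply is that the family is undefined, so the 15-pair count is only one reading. That is right, and it is why both readings are shown. Tukey applied to the three time-specific arm differences would even contain the T2-T1 contrast, with critical value 2.37 and power of 69% at 55 per arm and 87% at 83. Nothing in the SAP says this is meant.

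A reader might also infer that Tukey is redundant because the interaction test already guards the arm contrasts. The SAP does not say that the interaction opens the step, and the null it writes is equality over time. Dropping Tukey without naming the gate could raise the error rate to about 12%.

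**Conclusion.** The point holds as a defect of a supplementary analysis. The post hoc step lacks a defined gate and family. On the usual reading it omits the arm difference in T2-T1 change and costs 21 or 32 percentage points of power for an arm contrast at 55 per arm, and 12 or 21 at 83 (four or six cells). Set against a gated alternative at 55 per arm, the gain is roughly 11 to 32 points, depending on the family and the effect pattern. The primary analysis is untouched and the VO2peak conclusions are largely protected; the practical exposure is the objective 3 risk factors at T1 and T2.

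Assumptions: the documents give an effect size only for VO2peak at 6 months. The power figures carry over to a risk factor only at the same standardised difference, 3.0/√30.5 = 0.54 SD. The contrast correlations are assumed. The 5% family-wise error applies to the three arm contrasts within one outcome and only under a joint arm gate.

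**What to change.** In SAP section 6 (and section 7 by reference) and protocol 9.3:

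1. State whether T0 is an outcome or only the covariate in the MMRM.
2. Name the gate as a 2-df joint test of the arm effect at 0.05. This is the intervention-by-time test if T0 is modelled as an outcome. If T0 is only the covariate, it is the joint test of the T1 and T2 arm differences, not the 1-df interaction.
3. Replace Tukey with the mCR-minus-control contrasts for T1-T0, T2-T0 and T2-T1 from the same model. Always report them with 95% CIs and, when the gate is significant, test each at two-sided 0.05.

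The cost is a change of wording and a few contrast statements; no new data are needed. The downsides are that error control is per outcome only, with no protection across the several risk factors, and that within-arm comparisons become descriptive.

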### *Outcomes*

#### Cardiovascular risk factor control:

- Changes in lipid profile (T1-T2)
- Changes in HbA1C (T1-T2)
- Changes in lean body mass (T1-T2)
- Changes in blood pressure (T1-T2)

The differences between the randomisation groups on the secondary continuous outcomes will follow the same approach as described in section 6 Study objective 2.

All analyses of PP will be in parallel to the description of the above.

[figure not shown]

## 8. Study objective 4

The overall occurrence of MACE (cardiovascular mortality, all-cause mortality, near sudden cardiac death, ACS, CV intervention/surgery, CV hospital admission, CV emergency visit) in the intervention group is lower than in the control group at T1 and T2.

The cumulative incidences of the composite endpoint MACE and the elements from which it is constituted will be presented by group. We will compute the probability of survival free from MACE past given time points (6 months and 12 months) and the survival function will be plotted by intervention group in Kaplan-Meier survival curves. The Kaplan Meier curves will indicate the occurrence of MACE during 12 months of follow-up. Patients who do not experience an event or are lost to follow-up without an event are censored. We will test for differences in hazard rates between the *mCR* and control group using Cox regression analysis allowing the baseline hazard functions to differ between centres.

[figure not shown]

## 9. Study objective 5

Joining the *mCR* programme results in an improved general health (e.g. quality of life (SF-36v2: Physical and Mental Component Summary Score), level of depression (PHQ-9), level of anxiety (GAD-7) and dietary pattern (Mediterranean Diet Score)) in comparison to not joining the *mCR* programme after T1 and T2 in cardiac patients.

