## 7.6 Study procedures

After screening (medical history, physical examination including blood pressure, laboratory check, ECG, questionnaire [general health, disease history, physical activity, lifestyle]), and approval of the cardiologist, patients will be included in the study. Patients will undergo several tests at one testing day. Testing will be performed at T0, T1 and T2 (figure 2).

[figure not shown]

Figure 2. Study procedures

**Testing day: Blood samples, Physical Fitness and Questionnaires (2 hours) (See Appendix I-Schedule of events)****Blood samples**

Blood samples will be obtained for the analyses of a number of CVD risk parameters (e.g. HDL, LDL, HbA1C) and renal function.

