**Physical fitness**

Before the assessment of physical fitness, skinfold thickness will be determined (biceps, triceps, sub-scapular, supra-iliac) to calculate the lean body mass. (13)

Physical fitness level will be measured as the  $VO_{2peak}$  during an incremental maximal exercise test, using a continuous gas analyser. ECG and heart rate will be registered continuously and blood pressure will be measured at fixed intervals of 3 minutes. The test will be performed under supervision. The modality for the exercise test will be cycling. All tests will be performed by the same protocol. For patients who are not able to participate in a  $VO_{2peak}$  test, this test will be replaced by a 6 Minutes Walking Test. The testing modality chosen per centre at T0, will remain the same at T1 and T2. To ensure a safe environment in which the tests can be performed, the test will be performed to applicable guidelines and regulations within each participating centre.

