#### **4.2.2 Per protocol analysis population**

The per protocol population consists of all subjects who adhere to the major criteria in the protocol and who have a cardiopulmonary exercise test (CPET) test with sufficient quality of tests at T0, T1 and T2. For the intervention group this implies subjects who complied with the use of the smartphone (use of the smartphone on at least 4 days per week with a minimum of 30 minutes of activity per day with a total registration of 150 minutes of activity per week during 21 weeks) during the first 6 months of the study.

Sufficient quality of CPET is defined as follows: identical protocol used in tests to be compared, respiratory exchange ratio (RER)  $\geq 1.1$  (or, if RER  $< 1$ , if delta between T0 and T1 and/or T2  $\leq 0.05$ ), and test duration  $\geq 4$  min (excluding warm-up), no signs of mask leakage or other equipment failure by visual inspection of CPET data.

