### 5.1 Efficacy analysis of primary study endpoint

The primary efficacy analysis will compare the change in peak oxygen uptake ( $VO_{2peak}$ /kg) from baseline (T0) to the 6 months follow up (T1) between the intervention and control group in the full analysis set.

$VO_{2peak}$ /kg will be derived from CPET. Approximated  $VO_{2peak}$  will be calculated from 6MWT as described under the definitions (document "EU-CaRE & EU-CaRE RCT SAP definitions").

The primary endpoint is the change in  $VO_{2peak}$  level between baseline (T0) and at 6 months (T1). It will be tested whether this change is different in the *mCR* and the control group by means of linear mixed models with the intervention as a fixed effect. The effect of centre on the outcome is modelled with a random effect. In the analyses we will adjust for the baseline value of  $VO_{2peak}$ . The null hypothesis is that there is no difference in mean change in  $VO_{2peak}$  level between the randomised groups. The alternative hypothesis is that the mean change in  $VO_{2peak}$  level differs between the randomised groups.

A covariance structure will be selected from several plausible structures. The covariance matrix resulting in the lowest Bayesian information criterion (BIC) fit statistic will be chosen.

To assess, if the underlying assumptions behind the mixed-effects model analysis are fulfilled, we will investigate normal quantile plots of residuals, standardized residuals, and random effects.

The linear mixed-effects model approach handles missing data appropriately and therefore multiple imputation or other methods to handle missing data in regard to the primary outcome will not be used. If necessary, the outcome variable will be transformed to obtain a normal distribution.

[figure not shown]

In case the groups differ on baseline values or other possibly confounding variables, the difference in change in  $VO_{2peak}$  level between baseline and 6 months between the intervention groups will be tested by means of linear mixed models analysis with centre as a random effect in which we will control for relevant confounders by adding covariates to the model. We will conclude a statistical significant difference in change in  $VO_{2peak}$  level between the *mCR* and control group when the two-sided p-value of the test statistic after adjustment for confounders is less than 0.05.

All analyses of PP will be in parallel to the description of the above.

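### The per-protocol analyses of lipids, HbA1C, lean body mass and blood pressure drop adherent patients for exercise-test failures that have no bearing on these outcomes

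*Combined protocol and SAP*

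**What the plan says.** SAP 4.2.2 sets up a single per-protocol (PP) population. In both arms, members must meet the protocol's major criteria, which are not listed there, and be patients "who have a cardiopulmonary exercise test (CPET) test with sufficient quality of tests at T0, T1 and T2". Adequate quality means the same test protocol in the tests compared, a rule on the respiratory exchange ratio (RER), at least 4 minutes of exercise beyond warm-up, and "no signs of mask leakage or other equipment failure by visual inspection of CPET data". One further condition applies to one arm only: "For the intervention group this implies subjects who complied with the use of the smartphone".

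SAP 7 (objective 3) names lipids, HbA1C, lean body mass and blood pressure, and ends: "All analyses of PP will be in parallel to the description of the above". SAP 18 extends the PP repeat to the primary and secondary endpoints in general. It calls the analysis supportive and gives its purpose as showing whether the treatment works in patients who comply. No section offers a PP set without the CPET condition.

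On measurement, protocol 7.6 states "Blood samples will be obtained for the analyses of a number of CVD risk parameters" and, for lean body mass, "Before the assessment of physical fitness, skinfold thickness will be determined". Blood pressure belongs to the physical examination in protocol Appendix I. For patients who cannot do the VO2peak test, "this test will be replaced by a 6 Minutes Walking Test". SAP 5.1 keeps those patients in the full analysis, because an approximated VO2peak "will be calculated from 6MWT as described under the definitions".

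**The concern.** The CPET condition makes sense for VO2peak, where a leaking mask or a very short test invalidates the measurement. It says nothing about whether a cholesterol value or a skinfold reading is valid, or whether the patient followed the programme. Applied to SAP 7, it removes patients who complied and whose outcome was properly measured.

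Two things are at stake, both within the supportive analysis. The first is precision: usable observations are discarded. The second is meaning: the result no longer describes those who complied, the question set in SAP 18, but those who complied and also produced three acceptable CPETs.

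**Working it through.** **Step 1: does the condition bear on the outcome?**

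| Outcome (SAP 7) | How it is measured | Uses CPET data? |
|---|---|---|
| Lipids, HbA1C | Blood sample (protocol 7.6) | No |
| Lean body mass | Skinfolds, before the fitness test (protocol 7.6) | No |
| Blood pressure | Physical examination (protocol Appendix I) | No |

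**Step 2: who is dropped?** Under SAP 4.2.2, a patient leaves the PP set for all four outcomes after one inadequate CPET at any visit. A patient who did a six-minute walk test in place of a CPET cannot enter at all, although the protocol provides for that substitution and SAP 5.1 keeps the patient in the full analysis. SAP 7 follows the methods of SAP 6, which include a repeated-measures model that can use incomplete visits. The PP rule still removes the whole patient.

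**Step 3: is the loss selective?** Excluding walk-test patients, requiring at least 4 minutes of exercise and requiring three adequate tests all point towards under-representing frailer patients. The RER rule is less clear. It also accepts a test with RER below 1 if the change between visits is at most 0.05, so by itself it does not strictly select the fit. Mask leakage has no evident link to fitness. Under-representation of frailer patients is therefore likely but not demonstrated.

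**Step 4: how much precision is lost?** The documents state neither a pass rate nor a PP sample size, so there is no figure of theirs to reproduce. The following is an illustration.

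- Let *q* be the proportion of CPETs that pass at each visit, among patients who otherwise qualify and have the outcome measured. Assumed values: 0.70, 0.80, 0.90.
- Retention *r* is the proportion with all three tests adequate. If failures fall on the same patients every time, *r* = *q*. If they are independent across visits, *r* = *q*³.
- CI width is proportional to 1/√n, so the widening is 1/√*r*. This assumes equal retention in both arms and an unchanged outcome SD.

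| *q* | *r* = *q* | Widening | *r* = *q*³ | Widening |
|---|---|---|---|---|
| 0.70 | 0.700 | 1/√0.700 = 1.20 | 0.343 | 1/√0.343 = 1.71 |
| 0.80 | 0.800 | 1/√0.800 = 1.12 | 0.512 | 1/√0.512 = 1.40 |
| 0.90 | 0.900 | 1/√0.900 = 1.05 | 0.729 | 1/√0.729 = 1.17 |

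Positive but incomplete clustering falls between the two cases.

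For scale, SAP 3 plans for 83 evaluable patients per arm (119 × 0.70 = 83.3). Full clustering would leave 83*q* = 58.1, 66.4 or 74.7 per arm, and independence 83*q*³ = 28.5, 42.5 or 60.5. These counts ignore exclusions for smartphone non-compliance, which would lower the intervention-arm number further.

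**The case against.** The strongest reply is that the plan already gives this analysis little weight. SAP 4.2.1 bases the main analyses on the full analysis population. SAP 18 says the PP comparison is restricted to ideal patients and cannot be unbiased. SAP 4.5 reports the number in each analysis set by group, and SAP 4.6.1 summarises baseline data for the PP set as well as the full set. A reader will therefore see how many patients are lost and whether those retained differ. All of this stands and limits the importance of the point. However, SAP 18 attributes the bias to non-random compliance and does not mention selection by CPET quality. A total per set also does not show which criterion removed whom.

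A common set is also defensible, since VO2peak and risk-factor results can then be read in the same patients. That stands as a reason to show the common-set result, but not as a reason to show it alone.

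A third reply is that, without the CPET condition, controls are hardly selected while intervention patients are selected for compliance. The imbalance is real, but it comes from the smartphone rule already in SAP 4.2.2. A CPET filter applied to both arms does not repair it.

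On size, the independent-failure figures are the pessimistic end. Walk-test use and low fitness are lasting traits, so failures probably cluster. All tests share one testing day (protocol 7.6), so a patient who misses a visit will mostly lack laboratory and skinfold data too, and that loss should not be charged to the CPET rule.

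A reader might go further and infer that the PP set contains only patients capable of three near-maximal tests, or that half or more of the patients will be lost. The documents support neither. The RER rule has its alternative branch, and no pass rate or walk-test share is given.

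**Conclusion.** The point holds as a limited flaw in a supportive analysis. Followed as written, the SAP excludes protocol-adherent patients with valid outcome data from the PP analyses of lipids, HbA1C, lean body mass and blood pressure. That exclusion is certain for any patient with a walk test in place of a CPET, or with one inadequate CPET. The number affected is unknown. Over assumed pass rates of 70% to 90%, the unnecessary widening of the confidence intervals ranges from about 1.05 to 1.71, depending mainly on how far failures cluster within patients. Under-representation of frailer patients is probable but inferred.

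It would be wrong to conclude that the answer to objective 3 is biased. The full-analysis results do not depend on this set. Making the change is worthwhile but not essential.

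**What to change.** In SAP 4.2.2, limit the CPET-quality condition to VO2peak outcomes. For the SAP 7 outcomes, and for any other endpoint not derived from CPET that is analysed per protocol under SAP 18, define membership by three conditions:

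- adherence to the major protocol criteria, which should be listed;
- smartphone compliance in the intervention arm, as already defined;
- availability of the outcome concerned.

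Report exclusions per criterion by arm. State which PP flag the per-protocol subgroup in SAP 4.8 uses, since there would now be two.

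The cost is a short addition to the SAP, a second population flag and one extra table. No new data are needed and the primary analysis is unchanged. The drawback is that PP results for VO2peak and for risk factors would come from different patients. The common-set result can be shown alongside for that comparison. The intervention arm would still be selected for compliance while controls are not, so the analysis must remain supportive.
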